## Abstract

**Background::**

Treatment for most patients with head and neck cancers includes ionizing radiation with or without chemotherapy. This treatment causes irreversible damage to salivary glands in the irradiation field accompanied by a loss of fluid-secreting acinar cells and a considerable decrease of saliva secretion. There is currently no adequate conventional treatment for this condition. In recent years, we developed an effective culture method to enhance the anti-inflammatory and vasculogenic phenotypes of peripheral blood mononuclear cells (PBMNCs), and such effectively conditioned PBMNC (E-MNC) therapy has shown promising improvements to the function of radiation-injured salivary glands in preclinical studies. However, the safety and effect of E-NMC therapy have yet assessed in human. The objective of this ongoing first-in-man study is to assess the safety, tolerability, and in part the efficacy of E-MNC therapy for treating radiation-induced xerostomia.

**Methods/design::**

This phase 1 first-in-man study is an open-label, single-center, two-step dose escalation study. A total of 6 patients, who had no recurrence of head and neck cancer over 5 years following radiation therapy and suffered from radiation-induced xerostomia, will receive a transplantation of E-NMCs derived from autologous PBMNCs to a submandibular gland. The duration of the intervention will be 1 year. To analyze the recovery of salivary secretion, a gum test will be performed. To analyze the recovery of atrophic salivary glands, computed tomography (CT), and magnetic resonance imaging (MRI) of salivary glands will be conducted. The primary endpoint is the safety of the protocol. The secondary endpoints are the changes from baseline in whole saliva secretion and salivary gland atrophy.

**Discussion::**

This will be the first clinical study of regenerative therapy using E-MNCs for patients with severe radiation-induced xerostomia. The results of this study are expected to contribute to developing the low-invasive cell-based therapy for radiation-induced xerostomia.

**Trial registration::**

This study was registered with the Japan Registry of Clinical Trials (http://jrct.niph.go.jp) as jRCTb070190057.

## Introduction

1

Treatment with radiotherapy either alone or in combination with surgery and/or chemotherapy for head and neck cancers causes a loss of fluid-secreting acinar cells, and this adverse effect gives rise to irreversible damage to salivary gland function in 63% to 93% of patients.^[1]^ Therefore, such patients usually suffer considerable morbidity, because dysfunction of salivary glands leads to severe xerostomia (dry mouth).^[1,2]^ Xerostomia frequently causes severe dental caries, aggravation of periodontal disease, oropharyngeal infections, and diminished mucosal wound healing.^[3]^ These symptoms increase the incidence of dysphagia and severely impact patient quality of life.^[4]^ Recently, to reduce radiation damage to salivary glands, approaches such as brachytherapy, intensity-modulated radiation therapy (IMRT), and heavy particle beam therapy have shown merit, but a significant proportion of patients still experience salivary gland atrophy and hypofunction.^[5]^

Current pharmacological approaches for radiation-induced xerostomia, including sialagogues or saliva substitutes, aim to stimulate saliva secretion from the residual acinar cells or provide alternatives that mimic natural saliva. However, these approaches are usually not satisfactory, because their effectiveness is only temporary.^[6]^ Furthermore, although sialagogues such as pilocarpine hydrochloride, a cholinergic agonist, have been frequently used to relieve radiation-induced xerostomia, they include major limitations resulting from common side effects such as sweating and gastrointestinal upset.^[6,7]^ Thus, a significant improvement of these symptoms in patients has yet to be observed using current pharmacological approaches. Therefore, developing adequate treatments for the restoration of radiation-induced atrophic salivary glands is urgently required.

We recently developed a novel culture method for peripheral-blood mononuclear cells (PBMNCs) with serum-free medium containing 5 recombinant growth factors (stem cell factor, thrombopoietin, vascular endothelial growth factor, interleukin-6, and Flt-3 ligand), and found that this culture method can successfully enhance the anti-inflammatory and vasculogenic potential of PBMNCs in a short period (5–7 days).^[8]^ The resulting effectively conditioned PBMNCs (E-MNCs) contain an enriched population of definitive CD11b/CD206-positive (M2 macrophage-like) cells. When E-MNCs were injected intra-glandularly into a mouse model of radiation-induced atrophic salivary glands, salivary secretory function gradually recovered after 4 weeks post-irradiation (post-IR), and was 4-fold higher than that of non-transplanted model mice at 12 weeks post-IR. Enhanced green fluorescent protein (EGFP)-expressing E-MNCs were detected in a portion of vascular endothelium and perivascular gland tissues at 2 weeks post-IR, but only in microvessel walls at 3 weeks. Between 4 and 12 weeks post-IR, mRNA-expression and histological analyses revealed that E-MNC transplantation reduced the expression of inflammatory genes and increased the level of tissue regenerative activities such stem cell markers (c-Kit and Sca-1), cell proliferation, and blood vessel formation. At 12 weeks post-IR, the areas of acinar and ductal cells regenerated, and the glands had less fibrosis. Therefore, this effective conditioning of PBMNCs is a simple, rapid, and efficient method that provides a noninvasive source of therapeutic cells for regenerating radiation-injured atrophic salivary glands.

The objective of this phase 1 first-in-man study has been to assess the safety and in part the efficacy of an intra-glandular injection of autologous E-MNCs for treating radiation-induced atrophic salivary glands and xerostomia. In this article, we provide the detailed design of this clinical study, which is ongoing and is registered with the Japan Registry of Clinical Trials.

## Methods/design

2

### Study design

2.1

This study is a phase 1 first-in-man clinical trial to assess the safety, tolerability, and efficacy of E-MNC therapy for radiation-induced xerostomia. This study will be conducted at a single center (Nagasaki University Hospital). A total of 6 patients with radiation-induced xerostomia will receive transplantation of E-MNCs. A two-step protocol will be used: the first 3 patients will be classified as “step 1” and will each receive transplantation with a low dose (8 × 10^6^) of E-MNCs. The other 3 patients will be classified as the “step 2” group and will each receive transplantation with a high dose (2 × 10^7^) of E-MNCs. The duration of the study is 1 year. The study design is summarized in Figure 1.

**Figure 1 F1:**
[figure not shown]
Study design. E-MNCs are generated in a hematopoietic stem cell expansion medium containing recombinant human SCF, recombinant human Flt-3 ligand, recombinant human TPO, recombinant human VEGF, and recombinant human IL-6. CT = computed tomography, MRI *=* magnetic resonance imaging, PBMNCs *=* peripheral blood mononuclear cells, E-MNC *=* effective mononuclear cell, CPC *=* cell-processing center.

This study was approved by Kyushu University Certified Special Committee for Regenerative Medicine (NA8150001) and was registered with the Japan Registry of Clinical Trials (http://jrct.niph.go.jp) as jRCTb070190057. We will conduct this study in accordance with the principles of the Declaration of Helsinki and the Japan Good Clinical Practice guidelines and in compliance with the Ethical Guides for Medical Studies in Human Subjects (promulgated on December 22, 2014) and the Act on the Protection of Personal Information and related regulatory notifications.

### Inclusion criteria

2.2

Patients must meet all of the following requirements to be considered for entry in the study:

1.xerostomia after radiotherapy for head and neck cancer;2.it has been 5 years after that radiotherapy, with no recurrence of head and neck cancer (complete remission);3.the complaint of dry mouth and a gum test result of <10 ml/10 minute;4.atrophy of salivary gland confirmed by CT or MRI;5.has undergone scaling, received tooth brushing guidance, and has maintained good oral hygiene;6.age 20 to 75 years;7.written informed consent (IC) can be obtained from the patient him/herself;8.the patient has the intention and ability to visit a hospital; and9.has the intention to use barrier contraception during the study period.

### Exclusion criteria

2.3

The patients who participate in this study will be required to undergo blood collection for the isolation of PBMNCs. Patients who show low hemoglobin counts will thus be excluded: <12.5 g/dl for males and <12.0 g/dl for females when 200 ml blood collection is conducted, and <13.0 g/dl for males and <12.5 g/dl for females when >200 ml blood collection is conducted. The other major exclusion criteria are as follows:

1.xerostomia caused by a salivary gland tumor;2.any other malignancy or sepsis;3.severe autoimmune or endocrinological disease;coagulation abnormality (PT < 50% or outside the APTT range 23.5–42.5 seconds);4.positivity of syphilis test/HBV antigen/HCV antigen/anti-HTLV-1 antibody/anti-HIV antibody;5.liver dysfunction (higher or lower value of 2 biomarkers of liver function than the following criteria: AST 10–40 IU/L, ALT 5–45 IU/L);6.pregnancy;7.risk of allergy regarding the drug used in this study;8.allergy regarding penicillin G, amphotericin B, or streptomycin;9.transmissible spongiform encephalopathy;10.dementia;11.a psychiatric disorder such as depression;12.a smoking habit;13.being judged by the clinical investigator as an inappropriate patient for this study.

### Outcome measurements

2.4

Study visits will take place at baseline (approx. 1 month before the surgery) and on specified days after the surgery. The assessments are presented in Figure 2. CT and MRI of salivary glands will be performed at baseline and after 28, 56, 112, and 365 days. Using these imaging methods, the size of atrophic glands and the volume of atrophic tissues will be calculated. Panoramic radiographs will be taken at baseline and after 365 days. A physical examination including the oral cavity and a safety assessment will be performed at every visit. Gum tests to evaluate the quantities of salivary secretion at 14, 28, 56, 112, 168, 252, and 365 days are planned.

**Figure 2 F2:**
[figure not shown]
Treatment schedule and outcome measures. CT = computed tomography, MRI *=* magnetic resonance imaging, PBMNCs = peripheral blood mononuclear cells, E-MNC = effective mononuclear cell.

The primary endpoint is the safety/tolerability of the protocol. The safety assessment, which conducted by independent safety monitoring board, will be done by a two-step process. The first 3 enrolled patients will receive transplantation of a low dose of E-MNCs (8 × 10^6^), and their safety will be assessed at ≥4 weeks after the surgery. If there are no serious adverse events in any of these 3 patients, the next 3 patients enrolled will receive transplantation of a high dose of E-MNCs (2 × 10^7^), and their safety will be assessed.

The secondary endpoints are the change from baseline in salivary secretion assessed by gum tests and the change in salivary gland atrophy (i.e., the rate of atrophic parts in salivary glands, and the volume of atrophic glands) assessed based on the CT/MRI findings.

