### Adverse events (AEs)

2.5

All adverse events (AEs) that occur between the surgery and 1 year post-surgery will be recorded. If necessary, the investigators will administer treatments. A serious AE (SAE) is defined as any adverse reaction resulting in any of the following outcomes: a life-threatening condition or death; a condition that requires inpatient hospitalization or prolongation of an existing hospitalization, threatening to cause disability or death; a congenital anomaly; or a birth defect. All SAEs will be reported to the IRB and certificated committee for regenerative medicine by the responsible investigator.

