### Surgical method for the injection of E-MNCs in the submandibular gland

2.8

The surgical procedure will be performed with local anesthesia in an operating room. The sterile E-MNCs suspension (400 μl, 8 × 10^6^, or 2 × 10^7^) will be injected into a unilateral submandibular gland guided by ultrasound; 100 μl of the E-MNCs suspension will be injected in 4 areas of the submandibular gland to ensure an equal distribution of the suspension. The participants will be administered a pain reliever such as a non-steroidal anti-inflammatory drug (NSAID). Wound cleaning will be done the next day and after 1 week post-surgery.

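### The printed rule for moving to the high dose tests only for serious adverse events, so a severe treatment-related local reaction that is not serious would not hold a 2.5-fold escalation

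*Protocol article*

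**What the plan says.** All references are to the protocol article.

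- Section 2.4 (Outcome measurements) sets the endpoint: "The primary endpoint is the safety/tolerability of the protocol".
- The same section gives the assessment to an independent safety monitoring board in two steps. For the 3 patients at 8 × 10^6 cells, "their safety will be assessed at ≥4 weeks after the surgery".
- The condition for escalating follows: "If there are no serious adverse events in any of these 3 patients". If it is met, the next 3 patients are to receive 2 × 10^7 cells. The text gives no other condition.
- Section 2.5 (Adverse events) defines a serious adverse event (SAE) by its outcome: death or a life-threatening condition; "a condition that requires inpatient hospitalization or prolongation of an existing hospitalization, threatening to cause disability or death"; congenital anomaly or birth defect.
- Non-serious events are covered by "All adverse events (AEs) that occur between the surgery and 1 year post-surgery will be recorded" and are treated if necessary. Section 2.4 adds "A physical examination including the oral cavity and a safety assessment will be performed at every visit".
- Section 2.8 gives both doses in the same 400 μl, of which 100 μl portions "will be injected in 4 areas of the submandibular gland".

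**The concern.** Seriousness and severity are different things. Seriousness describes an event's outcome, such as death or admission. Severity describes its intensity. Tolerability depends largely on severity, yet the escalation rule looks only at seriousness.

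The gap is a severe local reaction to the injection (for example marked pain, swelling or infection of the gland) that is treated on an outpatient basis and threatens neither life nor disability. Such an event counts towards the primary endpoint but not towards the one dose decision in the trial.

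Local toxicity is a plausible dose-related harm here, because step 2 puts more cells into the same volume at the same number of sites. At stake is the protection of the 3 high-dose patients in a first-in-man study of a cell product whose processing method the Discussion (section 3) calls newly developed.

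**Working it through.** **1. Size of the step.** Inputs are the two doses (sections 2.1, 2.4 and 2.8), 400 μl in total and 4 injection areas (section 2.8).

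| | Low dose | High dose | Ratio |
|---|---|---|---|
| Cells in total | 8 × 10^6 | 2 × 10^7 | 2.5 |
| Cells per site (total / 4) | 2 × 10^6 | 5 × 10^6 | 2.5 |
| Cells per μl (total / 400) | 20,000 | 50,000 | 2.5 |

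**2. Does the SAE definition close the gap?** The punctuation before the words on threatened disability or death can be read in more than one way.

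- Broadest reading: admission, prolonged stay, threatened disability and threatened death each count alone. A severe reaction with none of these is still not an SAE.
- Narrowest reading: admission or prolonged stay counts only if disability or death is also threatened. The gap is then wider, since even some reactions that need admission drop out.

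No reading adds a category for severe or medically important events. The gap exists on every reading, and the broadest one is used from here on.

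**3. How the rule behaves.** Let p be the SAE rate per low-dose patient and q the rate of severe, treatment-related, non-serious events. The printed condition is met with probability (1 − p)^3. This does not contain q, so the condition is equally likely to be met whether such reactions are absent or occur in all 3 patients.

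**4. Illustration only.** The documents give neither p nor q. With p = 5% assumed, (1 − 0.05)^3 = 0.857. The probability that the condition is met although at least one patient had a severe non-serious event is:

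- 0.857 − (1 − p)^3(1 − q)^3 if the two kinds of event are independent;
- 0.857 − (1 − p − q)^3 if they never occur in the same patient.

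| Assumed q | Independent | Never in the same patient |
|---|---|---|
| 2% | 0.857 − 0.807 = 0.05 | 0.857 − 0.804 = 0.05 |
| 5% | 0.857 − 0.735 = 0.12 | 0.857 − 0.729 = 0.13 |
| 10% | 0.857 − 0.625 = 0.23 | 0.857 − 0.614 = 0.24 |
| 20% | 0.857 − 0.439 = 0.42 | 0.857 − 0.422 = 0.44 |

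The result depends almost entirely on the assumed q. The table shows how the rule works; it does not estimate the risk in this trial.

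**The case against.** **The article is a condensed account.** Grading scales, dose-limiting toxicity definitions and the board's remit often sit in the full protocol or a charter, and the two design figures are not shown. This limits the point to the article's text. It does not remove it, because the article prints a concrete decision rule, and that rule is narrow. If the full protocol holds a wider rule, the article misdescribes it and the same sentence needs correcting.

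**An independent board reviews safety.** This is the strongest objection, and it largely stands. A reader might infer that the trial would escalate automatically even after severe reactions in all 3 low-dose patients. The documents do not support that. The board is to assess these patients' safety, not merely count SAEs, and all adverse events are recorded. What remains is that the text gives the board no stated ground for holding escalation once the SAE condition is met.

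**The gap may be small.** The article does not say whether patients stay in hospital after the injection. If they do, an early severe reaction could prolong the stay and so become an SAE. The article also reports no dose-related local toxicity; the potential clinical risk it names is tumour growth and metastasis, which a severity rule at 4 weeks would hardly detect. Both points stand. They limit the scope of the concern without closing the gap.

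**The rule is already strict.** One SAE in 3 patients stops escalation, with no cohort expansion. That is true of SAEs, but it does nothing for severe events that are not serious. It is, however, a good reason not to add a second absolute bar. With p = 5% and q = 20% (assumed, independent), a rule that never escalates after any such event would leave step 2 unopened with probability 1 − 0.439 = 0.56, against 1 − 0.857 = 0.14 under the printed rule. A hold with board review avoids this.

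**Conclusion.** The point holds in a limited form. As printed, the escalation rule tests only part of the safety/tolerability endpoint. It leaves out severe treatment-related reactions that need no admission or longer stay and threaten neither life nor disability. The step that follows raises cell number and concentration at each injection site 2.5-fold; that figure comes directly from the stated doses and volumes.

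The conclusion rests on the wording of sections 2.4 and 2.5 and assumes that no wider rule exists in documents not shown. A reader might take the illustrative probabilities as evidence that the rule is unsafe, or as the chance of wrongly escalating. They are neither: every rate is assumed, and they ignore the board's judgement. This is a rule that should be widened, not a defect that invalidates the trial.

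**What to change.** Replace the escalation condition in section 2.4 with:

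> At 4 weeks or later after surgery, the independent board reviews all step-1 adverse events, graded by severity on a standard scale and assessed for relatedness. Any SAE stops escalation. Any severe (grade 3 or higher) treatment-related adverse event holds escalation until the board has reviewed it and explicitly agreed that the high dose may be given.

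Name the grading scale and say who attributes relatedness, since the article gives neither.

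**Cost.** No visit or test is added: events are already recorded, safety is already assessed at each visit, and the board already reviews step 1. The extra work is grading and attribution. Step 2 may be delayed or, if the board so decides, not opened. The size of this effect cannot be estimated from the documents.

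**Timing.** Section 2.10 puts the start of recruitment in April 2019 and its expected end in 2021, and does not say whether step 1 is complete. If the decision has already been taken, the change can no longer guide it. The trial report should then give the graded, attributed step-1 events and the board's reasons for its decision.

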This first-in-man phase 1 study aims to evaluate the safety and in part the efficacy of E-MNC therapy using an intra-glandular injection for patients who suffer from radiation-induced xerostomia. E-MNCs are obtained with a serum-free primary culture system in only 5 to 7 days after 100 to 240 ml of blood is collected, and then their suspensions can be injected directly into salivary glands without any surgical procedures. E-MNCs are considered to have low tumorigenicity, as found in pluripotent stem cells, because E-MNCs are composed of autologous blood cells such as lymphocytes, monocytes/macrophages, and their progenitors.^[8]^ Therefore, this strategy is thought to have low invasiveness and be applied easily and safely in the clinic. However, the cell processing method for E-MNCs is simple but newly developed. In addition, the transplantation of E-MNCs may have the potential risk of activating tumor growth and metastasis due to their vasculogenic properties. Therefore, we planned this clinical study as a phase 1 first-in-man two-step dose-escalation study to verify the safety of E-MNC therapy restricted to patients who have had no recurrence of head and neck cancer over 5 years following radiation therapy. As mentioned above, Grønhøj et al have used advanced adipose tissue-derived MSC therapy in a phase 1/2 trial for radiation-induced xerostomia.^[19]^ These studies will help improve the methodology for cell-based therapy and inform the design of subsequent studies on the safety and potential efficacy of this intervention.

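### The printed gate to the high dose counts only SAEs, so a tumor event judged unrelated, or not yet meeting a listed outcome, would not hold escalation

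*Protocol article*

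**What the plan says.** Section 2.4 (Outcome measurements) makes safety and tolerability the primary endpoint and gives its assessment to an independent safety monitoring board. Three patients receive the low dose and "their safety will be assessed at ≥4 weeks after the surgery". The rule then reads: "If there are no serious adverse events in any of these 3 patients, the next 3 patients enrolled will receive transplantation" at the high dose. No other escalation condition is printed.

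Section 2.5 (Adverse events) supplies the term on which the rule depends: "A serious AE (SAE) is defined as any adverse reaction resulting in any of the following outcomes". The outcomes are a life-threatening condition or death; "a condition that requires inpatient hospitalization or prolongation of an existing hospitalization, threatening to cause disability or death"; and a congenital anomaly or birth defect. There is no item for malignancy and none for a medically important event. The same section also says "All adverse events (AEs) that occur between the surgery and 1 year post-surgery will be recorded".

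The Discussion (section 3) notes that the cell-processing method is new and that "the transplantation of E-MNCs may have the potential risk of activating tumor growth and metastasis due to their vasculogenic properties". It presents the two-step escalation, "restricted to patients who have had no recurrence of head and neck cancer over 5 years following radiation therapy", as the response to both concerns. Section 2.2 carries the restriction into eligibility ("it has been 5 years after that radiotherapy, with no recurrence of head and neck cancer (complete remission"), and section 2.3 excludes other malignancies.

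**The concern.** The tumor risk is written into the entry criteria and into the reasons for the design, but not into the one decision that exposes three more cancer survivors to a higher cell number. The SAE definition covers tumor events only indirectly. Two things must be true before one counts: someone judges it a reaction to the treatment, and it already has one of the listed consequences.

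The first condition is the more awkward. In a patient with a history of head and neck cancer, the obvious explanation for a recurrence is the original disease. With three treated patients and no control group, no analysis could confirm or refute that attribution. A dose-escalation decision should not depend on a judgment that the trial cannot inform.

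**Working it through.** The article states no figure on this point that could be reproduced. The check is a reading of sections 2.4, 2.5 and 3 together, with two pieces of arithmetic for scale.

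**Dose step.** From section 2.1: 2 × 10^7 / 8 × 10^6 = 2.5.

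**What the gate counts.** Two phrases in the SAE definition can each be read in two ways.

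- *Reaction* may mean a causally related event. It may also be loose wording for event, which is plausible because the section heading and the defined term both speak of adverse events.
- The words on threatened disability or death may be a separate outcome. They may also qualify the hospitalization clause, which they follow after a comma.

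The four combinations give these results for a tumor event in a low-dose patient:

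1. Causal reading, threat qualifies hospitalization: the event passes the gate if it is judged unrelated. It also passes if it is not life-threatening and leads to no qualifying admission.
2. Causal reading, threat stands alone: the event passes if it is judged unrelated. If judged related, most tumor events would count.
3. Loose reading, threat qualifies hospitalization: attribution no longer matters. A small lesion found at a visit and managed as an outpatient still passes.
4. Loose reading, threat stands alone: a recurrent or metastatic cancer would ordinarily count at diagnosis, and little or nothing passes.

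So three of the four readings leave some gap, and the most generous one nearly closes it. The printed text does not say which is meant.

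**How often it could arise before the gate.** The minimum look is 4 weeks, or 28 days. At that minimum the three patients contribute 3 × 28 = 84 patient-days, against 3 × 365 = 1,095 over the full adverse-event follow-up, a ratio of 1,095 / 84 ≈ 13. The 84 days is a floor, because section 2.4 allows a later assessment and patients treated earlier will have longer follow-up. In patients selected for 5 years without recurrence, few tumor events would be expected in so short a period.

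**Why no percentage follows.** The share of tumor events that the gate would miss depends on the chance of being judged unrelated and the chance of meeting no listed outcome when found. How often the gap would arise depends also on the recurrence rate. The article gives none of these, so any percentage would only reflect values chosen by the reviewer.

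**The case against.** The best reply is that this is a condensed article and the full protocol may list gating events and board procedures. Sections 2.4 and 2.5 also contain real safeguards: an independent board, a physical examination including the oral cavity at every visit, and a record of all adverse events for a year. A recurrence would very probably be seen, and nothing tells the board to ignore it. On the most natural reading of a badly punctuated list, recurrent cancer may already be an SAE.

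Much of this stands, and it is why the point is minor. It does not remove the point. The article prints a complete rule, with a condition and a consequence, and prints the definition behind it. The comment is on how that rule is worded, not on a detail left to another document. Board review and complete recording mean that the event would be known, but they do not make it a reason to hold.

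A reader might go further and infer that the gate ignores tumor events, or that section 2.4 contradicts the Discussion. The documents support neither. Tumor events that meet the SAE definition do close the gate. The Discussion answers the risk with staged dosing plus restricted entry, and sections 2.2 to 2.4 deliver both.

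A reader might also infer that the 4-week minimum must be lengthened to wait for later scans. The article does not support that either: the stated purpose of the imaging is gland size and atrophy, and nothing in it quantifies what a wait would gain.

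**Conclusion.** The point holds as a narrow gap in a printed rule. Read literally, a recurrence, metastasis or new malignancy in a low-dose patient does not hold escalation if it is attributed to the original cancer or meets no listed outcome when found. Tumor activation is one of two stated reasons for escalating in two steps, so the rule should address it directly.

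The practical size is small and cannot be put as a number. Most recurrences would meet an outcome, few would appear by the time of the gate, and an independent board is in place. The conclusion rests on the printed text of sections 2.4 and 2.5. If the full protocol already provides for a hold on tumor events, only the wording of the SAE definition remains to be corrected. This is an improvement to consider, not a flaw that undermines the trial.

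**What to change.** In section 2.4, state: *Escalation to the high dose proceeds if there is no SAE in the 3 low-dose patients. Any recurrence, metastasis or new malignancy in these patients known before a high-dose injection, regardless of judged causality, holds high-dose injections until the independent safety monitoring board has reviewed it and decided whether to proceed.*

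In section 2.5, replace *adverse reaction* with *adverse event* in the SAE definition.

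The clause is a hold with a route to release, not an absolute bar, so one unrelated recurrence need not end the escalation. It needs no new visit, scan or fixed waiting time. The cost is a delay to dosing while the board reviews an event that may prove unrelated. The change in section 2.5 also means that an unrelated admission in a low-dose patient would count as an SAE at the gate, and the sponsor should accept that knowingly.

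Recruitment began in April 2019 (section 2.10), so step 1 may already have passed its gate. In that case the hold still applies to any high-dose injection not yet given. It has no gating role once the last one is done, because no higher dose follows.
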